### Eligibility criteria

Subjects will be recruited from the China Autism Rehabilitation Research Center, Beijing Boai Hospital, if they are aged between 2–10 years, with an ASD diagnosis according to the DSM-5 criteria. The majority of individuals with ASD who come to our hospital for treatment and hospitalization are between 2 and 10 years old, which ensures the feasibility of including children of this age group. We include pre-adolescent children to reduce the influence of pubertal development on the outcomes (e.g. biological outcomes). The statement of informed consent should be signed by a legal guardian. Both gender and education level are not limited. Exclusion criteria are as follows: 1) History of seizures or epilepsy; 2) Neurological or psychiatric disorders not associated with ASD; 3) Cardiac pacemakers, cochlear implant, and any metal inserted into the head; 4) Having undergone some neurosurgical procedures; 5) Currently participating in another randomized controlled trial; 6) Receiving non-invasive brain stimulation in the past 3 months; 7) Concomitant psychopharmacological medication or medication contraindicated for rTMS. Participants who are absent from two or more consecutive intervention sessions or a total of four sessions will be withdrawn from the study. Subjects will also be withdrawn from the study if they are unable to cooperate with the treatment or if their legal guardian is unwilling to continue with the trial. The study of a participant will end if he/she has a serious adverse reaction to the treatment, such as an epileptic seizure.

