### Intervention procedures

Twenty intervention sessions will be held over 4 consecutive weeks, with five sessions per week (Monday to Friday). A repetitive magnetic stimulator (Neurosoft LLC, [name]) and a figure-of-eight coil with a 70 mm diameter will be employed to administer iTBS over the left DLPFC (F3), following the 10–20 international EEG system (48). The subjects are required to wear a tight-fitting EEG cap, and the position of “F3” is marked using a mark pen. Three different sizes of EEG caps will be prepared for the purpose of target locating assistance, which will correspond to the following head circumferences: 46-50 cm (extra small), 50-54 cm (small), and 54-58 cm (medium). The magnetic coil was positioned at this point with an angle of approximately 45° to the interhemispheric line (49). A “sham coil” is employed to simulate the visual, auditory, and tactile aspects of rTMS without actually delivering any electromagnetic stimulation. The resting motor threshold of each participant was determined by stimulating the primary motor cortex until a 50 μV deflection of electromyogram or a visible twitch in the first dorsal interosseous muscle was identified in at least two of three trials (26, 50). One iTBS session consists of triplet 50 Hz pulses repeated in 5 Hz bursts for a total of 1800 pulses at 90% of the motor threshold (51). Sixty trains were applied in 2-second bursts with 8-second pauses. Previous research has found that three continuous sessions of iTBS with no interval (1800 pulses) over the primary motor cortex can reverse the effect from excitatory to inhibitory (52). Contrary to this motor cortex study, applying iTBS with 1800 pulses over the left DLPFC may act on DLPFC activity via the modulation of excitation/inhibition balance, which is similar to one regular session of iTBS (600 pulses) (53). The treatment will be administered in three sessions per day, with a 10-minute interval between each session (5400 pulses per day). The magnetic coil will be held by the experimenter as this is more comfortable for the subjects. During the rTMS administration, the subjects will be instructed to sit in a chair and refrain from moving. Children who are emotionally unstable or unable to remain seated are allowed to eat snacks, play with their favorite toys, or listen to music, while parents are encouraged to offer comfort and reassurance. Earplugs are provided for noise reduction. Younger children can be held by their parents or placed in a stroller for treatment. If adaptation remains challenging, parents are advised to bring their child to the treatment room daily over the next few days to acclimate them to the room environment and the noise and stimulation of TMS. For children who continue to be unable to tolerate treatment, they will be withdrawn from the trial. Once the child has acclimated to TMS treatment, eating snacks, playing with toys, or listening to music during the sessions will no longer be allowed. The children are allowed to rest between the three treatment sessions, during which they are free to play and interact with the parents and researchers. Furthermore, it is our intention to cultivate a positive relationship with the children.

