
### Assignment of interventions

This is a double-blind randomized clinical trial. The randomization of participants will be conducted using a computer-generated random list, based on the permutation block method with a random number generator. The ratio of participants allocated to each group will be 1:1. The allocation sequence was concealed by a research assistant using sealed, opaque envelopes that contained the treatment information prior to the study’s official commencement. Once the consent form and baseline measures have been completed, an envelope for a participant ID number will be provided to the rTMS therapist prior to the first iTBS session. The rTMS therapist is the sole individual responsible for determining the treatment method (iTBS or sham-iTBS), and he/she does not perform assessments or statistical analyses. It is imperative that other study researchers, participants, parents/guardians, and statistical analysts, remain completely blinded to the treatment condition. Any adverse or discomfort event will be recorded after each iTBS treatment session. If a participant experiences a serious adverse event, the blindness will be removed.

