### Outcome measures

For the first study objective, to determine feasibility and safety, we will report the recruitment rate, adherence rate, completion rate, and adverse reactions. The recruitment rate will be reported as the percentage of eligible ASD children who will participate in the study and the number of subjects recruited monthly over the recruitment period. The adherence rate will be measured by the proportion of participants who complete the intervention as planned. The completion rate will be assessed by the proportion of participants who complete all assessments and follow-ups. Safety will be assessed by comparing the rates of drop-outs attributed to adverse events and the rates of serious adverse events. For the second study objective, to determine the potential efficacy of the iTBS intervention on ASD, our endpoints include the Autism Behavior Checklist (ABC), Social Responsiveness Scale, 2nd Edition (SRS-2), Childhood Autism Rating Scale (CARS), Autism Treatment Evaluation Checklist (ATEC) and the Repetitive Behavior Scale-Revised (RBS-R). The ABC scale consists of 57 items that involve a range of typical autistic behaviors. These items are categorized into five domains including relating, sensory, language, body use and object manipulation, and social and self-help. Each item contained its own score ranging from 1 to 4 points according to the item weights, and higher total scores indicate more severe ASD symptoms (56) The SRS-2 is a norm-referenced quantitative assessment comprising 65 items pertaining to children’s behavioral characteristics. Parents or caregivers are required to rate five subdomains, namely social awareness, social cognition, social communication, social motivation, and restricted repetitive behaviors (57). The CARS was developed as an observational rating scale to capture ASD symptoms through parent/carer interviews, observations, and case reviews. Each item is scored from 1 to 4, with 1 representing appropriate behavior and 4 representing behavior that deviates severely from normal criteria, so higher total scores indicate more severe ASD symptoms. This tool can be utilized to display the overall symptom severity of ASD (58). The participant’s parent needs to complete the ATEC questionnaire, which is comprised of four subscales (speech/language communication, sociability, sensory/cognitive awareness, and physical/health/behavior). The ATEC has been used to measure treatment effects, with a lower score indicating a lower severity of ASD symptoms (59). The RBS-R was a valid tool for assessing repetitive and stereotypic behaviors in children with ASD, including six parts: stereotyped behaviors (6 items), self-injurious behaviors (8 items), obsessive-compulsive behaviors (8 items), ritualistic behaviors (6 items), fixation behaviors (11 items), and restrictive behaviors (4 items). The scale uses a 0-3 scoring system: 0 for no behavioral problems, 3 for severe, 2 for moderate, and 1 for mild (60).

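### Children who miss sessions or cannot tolerate stimulation leave the study, not only the treatment, so their end-of-treatment outcomes are lost and the completion rate cannot exceed retention

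*Protocol article*

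**What the plan says.** The Eligibility criteria set an attendance rule: "Participants who are absent from two or more consecutive intervention sessions or a total of four sessions will be withdrawn from the study". The same section adds "Subjects will also be withdrawn from the study if they are unable to cooperate with the treatment" and, for serious reactions, "The study of a participant will end if he/she has a serious adverse reaction to the treatment". Intervention procedures repeats the principle for children who do not adapt: "For children who continue to be unable to tolerate treatment, they will be withdrawn from the trial".

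Under Assignment of interventions, allocation follows consent and baseline measures: "an envelope for a participant ID number will be provided to the rTMS therapist prior to the first iTBS session". Withdrawals for missed sessions, non-cooperation or intolerance therefore happen after randomisation.

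Outcome measures lists adherence (finishing the intervention as planned) and completion as separate feasibility outcomes. On the second it says: "The completion rate will be assessed by the proportion of participants who complete all assessments and follow-ups". The abstract gives baseline and end of intervention as the assessment times. The Data analysis plan fits a mixed-effects model with group and time, and names a follow-up time as well.

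Intervention procedures uses *session* in two senses. One is the daily visit: "Twenty intervention sessions will be held over 4 consecutive weeks, with five sessions per week (Monday to Friday". The other is a block within a day: "The treatment will be administered in three sessions per day, with a 10-minute interval between each session (5400 pulses per day".

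**The concern.** The rules tie staying in the study to staying on treatment. A child who stops stimulation also leaves outcome assessment, although nothing about stopping treatment prevents the scales, saliva sample, EEG or fNIRS from being done at week 4.

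Two things are at stake. The first is the efficacy comparison. Week-4 data come only from children who attended, cooperated and tolerated treatment. If active stimulation is harder to tolerate than sham, and children who do badly are the ones who leave, the active arm loses its worse outcomes. Such a child contributes one baseline value. A mixed model can use that value but learns nothing from it about the missing week-4 score. A follow-up visit would not help, since a withdrawn child misses that too.

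The second is feasibility. The pilot is meant to inform a larger trial, which needs to know how many children would still attend outcome visits after stopping treatment. Under these rules that share cannot be observed.

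**Working it through.** **1. The protocol's own figure.** Sample size and recruitment gives 40 children (20 per arm), 15% dropout and a target of 48. Overall, 40 / (1 − 0.15) = 47.06. Per arm, 20 / 0.85 = 23.53, rounded up to 24, and 2 × 24 = 48. The figure reproduces. At the 15% allowance, 48 × 0.85 = 40.8 children would have week-4 data. If all randomised children were assessed, up to 48 could.

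**2. How many the attendance rule removes.** The documents give no absence rate, so take an assumed probability *p* of missing a treatment day, independent across 20 days. If a session is a daily visit, a child stays in with at most three absences, none adjacent. There are C(21 − k, k) ways to place k such absences, that is 1, 20, 171 and 816 for k = 0 to 3, so

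P(withdrawn) = 1 − Σ C(21 − k, k) p^k (1 − p)^(20 − k), k = 0 to 3.

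At p = 0.05 the terms are 0.358 + 0.377 + 0.170 + 0.043 = 0.948, so 5.2% are withdrawn. If a session is one of the three daily blocks, one missed day is already three consecutive absences, and P(withdrawn) is at least 1 − (1 − p)^20. At p = 0.05 this is 64.2%.

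| Assumed p per day | Withdrawn, daily reading | Of 48 | Retained with fewer than 20 visits | Withdrawn, three-per-day reading |
|---|---|---|---|---|
| 2% | 0.8% | 0.4 | 32.5% | 33.2% |
| 5% | 5.2% | 2.5 | 59.0% | 64.2% |
| 8% | 13.8% | 6.6 | 67.3% | 81.1% |
| 10% | 21.6% | 10.3 | 66.3% | 87.8% |

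The meaning of *session* therefore decides whether the rule removes few children or most of them. The fourth column (daily reading) also shows that many retained children could miss a visit and still be assessed.

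**3. Bias in the week-4 comparison.** This was a large simulation (400,000 per arm) with no true effect, a score on which higher is worse, SD 1, and an assumed baseline-to-week-4 correlation of 0.6. The log-odds of withdrawal rise by 0, 1 or 2 per unit of the part of the week-4 score that baseline does not predict. The analysis regresses week 4 on baseline in retained children and predicts at the mean baseline of all randomised children. This stands in for a missing-at-random mixed model with two visits.

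| Withdrawn, active vs sham | Slope 0 | Slope 1 | Slope 2 |
|---|---|---|---|
| 15% vs 15% | about 0 | about 0 | about 0 |
| 20% vs 10% | about 0 | 0.055 SD | 0.084 SD |
| 30% vs 10% | about 0 | 0.109 SD | 0.170 SD |

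Non-zero entries favour iTBS. Retained children alone, without the baseline adjustment, give 0.054 and 0.085 for the second row and 0.108 and 0.170 for the third. The model does not reduce the bias. The 20% vs 10% row averages (20 + 10) / 2 = 15%, the protocol's overall allowance. The 30% vs 10% row averages 20%, above it.

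**4. Completion and retention.** A withdrawn child cannot complete all assessments. Hence completion rate ≤ 1 − withdrawal rate, whatever the family would have been willing to attend.

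**The case against.** The strongest reply is that bias is possible but not shown. The rules apply alike to both arms, children and parents are blinded, and the sham coil imitates the look, sound and feel of stimulation. Several triggers, such as missed visits or not adapting to the room and noise, may be equally common in both arms. No figure in the article supports an arm difference or a link with outcome. This stands: between-arm bias needs both, and the simulation gives about zero without them.

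Size is a fair point too. With 20 per arm the standard error of a raw difference is √(2/20) = 0.32 SD, so the largest bias above is 0.17 / 0.32, about half a standard error. Efficacy is the second objective, and unequal withdrawal would be visible because feasibility and safety rates are compared between groups. But seeing unequal loss does not recover the missing outcomes.

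It can also be said that analysis sets and missing-data handling belong to an analysis plan not shown here. That is right for the analysis set, but not for data collection: no analysis plan can restore assessments that a stated rule prevents.

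Three stronger readings are tempting and not supported:
- A reader might infer a completers-only analysis. The Data analysis plan names no such set and does not discard baseline values.
- A reader might infer that completion and adherence are the same measure. On the daily-visit reading, a child may miss up to three non-consecutive sessions and still complete, and a fully adherent child may fail an EEG, fNIRS, saliva or scale assessment.
- A reader might apply the 15% dropout to the active arm alone. With an assumed correlation of 0.3 to 0.5 between intolerance and worse change, that gives a shift of 0.08 to 0.14 SD. But the 15% is an overall allowance, and 15% vs 0% is only 7.5% overall.

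**Conclusion.** The point holds as a should-fix. The protocol removes randomised children from the study for absence, non-cooperation or intolerance, and the article provides no end-of-treatment assessment for them. Any withdrawal that differs by arm and relates to the unseen outcome is then beyond correction. Its size is about 0.05 to 0.08 SD at 20% vs 10% and 0.11 to 0.17 SD at 30% vs 10%. These figures rest on the assumed withdrawal rates, the assumed correlation of 0.6 and the assumed strength of selection. They are illustrations, not predictions.

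The feasibility consequence needs no assumption about arms: completion is capped by retention, and assessment attendance after stopping treatment goes unobserved. Separately, the absence threshold has two possible meanings, with very different consequences for how many children it removes.

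**What to change.** - Separate stopping treatment from leaving the study in Eligibility criteria and Intervention procedures. The criteria for stopping treatment stay as they are.
- Keep children who stop treatment under those criteria on the scheduled end-of-treatment scales, saliva, EEG and fNIRS, unless the guardian withdraws consent.
- Include these data in the mixed model by assigned arm.
- Define the completion rate over all randomised children, independently of sessions attended.
- Reconcile the two uses of *session* so that the absence threshold has one meaning. Which meaning is intended is for the investigators to state.

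The recruitment target of 48 does not change. The cost is a short amendment, some reminders or extra trips for families, and possibly a slightly less favourable efficacy estimate.

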### Intervention procedures

Twenty intervention sessions will be held over 4 consecutive weeks, with five sessions per week (Monday to Friday). A repetitive magnetic stimulator (Neurosoft LLC, [name]) and a figure-of-eight coil with a 70 mm diameter will be employed to administer iTBS over the left DLPFC (F3), following the 10–20 international EEG system (48). The subjects are required to wear a tight-fitting EEG cap, and the position of “F3” is marked using a mark pen. Three different sizes of EEG caps will be prepared for the purpose of target locating assistance, which will correspond to the following head circumferences: 46-50 cm (extra small), 50-54 cm (small), and 54-58 cm (medium). The magnetic coil was positioned at this point with an angle of approximately 45° to the interhemispheric line (49). A “sham coil” is employed to simulate the visual, auditory, and tactile aspects of rTMS without actually delivering any electromagnetic stimulation. The resting motor threshold of each participant was determined by stimulating the primary motor cortex until a 50 μV deflection of electromyogram or a visible twitch in the first dorsal interosseous muscle was identified in at least two of three trials (26, 50). One iTBS session consists of triplet 50 Hz pulses repeated in 5 Hz bursts for a total of 1800 pulses at 90% of the motor threshold (51). Sixty trains were applied in 2-second bursts with 8-second pauses. Previous research has found that three continuous sessions of iTBS with no interval (1800 pulses) over the primary motor cortex can reverse the effect from excitatory to inhibitory (52). Contrary to this motor cortex study, applying iTBS with 1800 pulses over the left DLPFC may act on DLPFC activity via the modulation of excitation/inhibition balance, which is similar to one regular session of iTBS (600 pulses) (53). The treatment will be administered in three sessions per day, with a 10-minute interval between each session (5400 pulses per day). The magnetic coil will be held by the experimenter as this is more comfortable for the subjects. During the rTMS administration, the subjects will be instructed to sit in a chair and refrain from moving. Children who are emotionally unstable or unable to remain seated are allowed to eat snacks, play with their favorite toys, or listen to music, while parents are encouraged to offer comfort and reassurance. Earplugs are provided for noise reduction. Younger children can be held by their parents or placed in a stroller for treatment. If adaptation remains challenging, parents are advised to bring their child to the treatment room daily over the next few days to acclimate them to the room environment and the noise and stimulation of TMS. For children who continue to be unable to tolerate treatment, they will be withdrawn from the trial. Once the child has acclimated to TMS treatment, eating snacks, playing with toys, or listening to music during the sessions will no longer be allowed. The children are allowed to rest between the three treatment sessions, during which they are free to play and interact with the parents and researchers. Furthermore, it is our intention to cultivate a positive relationship with the children.

### Assignment of interventions

This is a double-blind randomized clinical trial. The randomization of participants will be conducted using a computer-generated random list, based on the permutation block method with a random number generator. The ratio of participants allocated to each group will be 1:1. The allocation sequence was concealed by a research assistant using sealed, opaque envelopes that contained the treatment information prior to the study’s official commencement. Once the consent form and baseline measures have been completed, an envelope for a participant ID number will be provided to the rTMS therapist prior to the first iTBS session. The rTMS therapist is the sole individual responsible for determining the treatment method (iTBS or sham-iTBS), and he/she does not perform assessments or statistical analyses. It is imperative that other study researchers, participants, parents/guardians, and statistical analysts, remain completely blinded to the treatment condition. Any adverse or discomfort event will be recorded after each iTBS treatment session. If a participant experiences a serious adverse event, the blindness will be removed.

### Sample size and recruitment

Forty children diagnosed with ASD will be included in total (iTBS group, n = 20; sham group, n = 20). Whilst a formal sample size calculation is not required in a pilot study (54), it is recommended that a sample size of between 15 and 20 participants is maintained for the purpose of conducting a subsequent full-scale study (55). In consideration of a potential dropout rate of 15%, the objective was to recruit a total of 48 participants. Nonetheless, we will endeavor to recruit a greater number of participants if feasible within the time and resources available. All participants will be recruited from the China Autism Rehabilitation Research Center, Beijing Boai Hospital, where advertisements will be posted to attract potential participants. One researcher will conduct the recruitment process, during which he/she will document the participants’ medical histories, including past and current medical conditions.

### Outcome measures

For the first study objective, to determine feasibility and safety, we will report the recruitment rate, adherence rate, completion rate, and adverse reactions. The recruitment rate will be reported as the percentage of eligible ASD children who will participate in the study and the number of subjects recruited monthly over the recruitment period. The adherence rate will be measured by the proportion of participants who complete the intervention as planned. The completion rate will be assessed by the proportion of participants who complete all assessments and follow-ups. Safety will be assessed by comparing the rates of drop-outs attributed to adverse events and the rates of serious adverse events. For the second study objective, to determine the potential efficacy of the iTBS intervention on ASD, our endpoints include the Autism Behavior Checklist (ABC), Social Responsiveness Scale, 2nd Edition (SRS-2), Childhood Autism Rating Scale (CARS), Autism Treatment Evaluation Checklist (ATEC) and the Repetitive Behavior Scale-Revised (RBS-R). The ABC scale consists of 57 items that involve a range of typical autistic behaviors. These items are categorized into five domains including relating, sensory, language, body use and object manipulation, and social and self-help. Each item contained its own score ranging from 1 to 4 points according to the item weights, and higher total scores indicate more severe ASD symptoms (56) The SRS-2 is a norm-referenced quantitative assessment comprising 65 items pertaining to children’s behavioral characteristics. Parents or caregivers are required to rate five subdomains, namely social awareness, social cognition, social communication, social motivation, and restricted repetitive behaviors (57). The CARS was developed as an observational rating scale to capture ASD symptoms through parent/carer interviews, observations, and case reviews. Each item is scored from 1 to 4, with 1 representing appropriate behavior and 4 representing behavior that deviates severely from normal criteria, so higher total scores indicate more severe ASD symptoms. This tool can be utilized to display the overall symptom severity of ASD (58). The participant’s parent needs to complete the ATEC questionnaire, which is comprised of four subscales (speech/language communication, sociability, sensory/cognitive awareness, and physical/health/behavior). The ATEC has been used to measure treatment effects, with a lower score indicating a lower severity of ASD symptoms (59). The RBS-R was a valid tool for assessing repetitive and stereotypic behaviors in children with ASD, including six parts: stereotyped behaviors (6 items), self-injurious behaviors (8 items), obsessive-compulsive behaviors (8 items), ritualistic behaviors (6 items), fixation behaviors (11 items), and restrictive behaviors (4 items). The scale uses a 0-3 scoring system: 0 for no behavioral problems, 3 for severe, 2 for moderate, and 1 for mild (60).

Salivary levels of oxytocin, growth hormone, IGF-1, and IGFBP-3 are measured by ELISA to reflect the biochemical response to treatments. A number of studies have demonstrated that the ELISA is capable of testing the concentration of oxytocin, growth hormone, IGF-1, and IGFBP-3 in human saliva (61–63). The ELISA kits are purchased from Shanghai Enzyme-linked Biotechnology Co., Ltd. (Shanghai, China). The parents/legal guardians were requested to ensure that their children refrained from eating, drinking, and oral cleaning for at least an hour before saliva collection. Subjects were instructed to spit at least 0.5ml of saliva into a disposable saliva collector. If a child is unable to carry out this instruction, the researchers will use a disposable pipette to extract his/her saliva. To eliminate any potential bias due to circadian rhythms, all salivary samples were collected between 4 and 5 p.m. Each sample was centrifuged and the resulting supernatant was divided into Eppendorf tubes and frozen at -80°C. At the end of the trial, the saliva samples will be irrevocably destroyed.

Resting-state EEGs will be recorded for 10 minutes using the CURRY 8.0 software in a 64-channel Neuroscan system (Compumedics Neuroscan, Victoria, Australia). An EEG cap with saline electrodes is used (GREENTEK, Wuhan, China) based on the international 10-20 system, which is easy to apply and does not necessitate gel applications. The data are acquired at a sampling rate of 1 kHz, and the impedances are maintained at a level below 50 kΩ. All the children need to be awake and relaxed during the EEG recordings. Three types of caps (extra small, small, and medium) will be prepared for them.

A fNIRS system (NirSmart-6000A, Danyang HuiChuang Medical Equipment Co., Ltd., Zhenjiang, China) is used to measure the spontaneous fluctuations in hemoglobin concentration in children with ASD at the resting state. The absorptions of three wavelengths (780nm, 805nm, and 830nm) of near-infrared light are measured with a sampling rate of 14.286 Hz (i.e. 70-ms temporal resolution) and subsequently transformed into concentration changes of oxyhemoglobin, deoxyhemoglobin, and total hemoglobin by means of the modified Beer-Lambert law. Fifty-four channels (24 light sources and 16 detectors) mainly covered the frontal, temporal, and occipital lobes, which were determined according to the international 10-20 system (**Figure 3**). All participants will be instructed to sit quietly for 8 minutes. If they are restless, a research assistant will try to comfort them. Three types of caps (extra small, small, and medium) will be prepared for them.

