**Methods:**

A randomized controlled pilot trial with a 4-week intervention will be conducted. Forty children with ASD will be randomized into either the intervention or control group. The intervention group will receive 5400-pulse iTBS per day, while the control group will receive sham iTBS. Feasibility will be evaluated through recruitment, intervention adherence, and assessment completion. Safety will be assessed by comparing the rates of drop-outs attributed to adverse events and the rates of serious adverse events The efficacy outcomes include the Autism Behavior Checklist, Social Responsiveness Scale, 2nd Edition, Childhood Autism Rating Scale, Autism Treatment Evaluation Checklist and Repetitive Behavior Scale-Revised. Resting-state electroencephalogram and functional near-infrared spectroscopy will be employed to quantify alterations in functional brain connectivity and cerebral haemodynamics. Salivary levels of oxytocin, growth hormone, insulin-like growth factor 1, and insulin-like growth factor binding protein 3 are measured to reflect the biochemical response to iTBS. These indicators will be assessed at baseline and at the end of the intervention.

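### The completion rate is one all-or-nothing proportion over eight different assessments, so it cannot show which of them are feasible for the larger trial

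*Protocol article*

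**What the plan says.** The Abstract (Methods) names three strands of feasibility: "Feasibility will be evaluated through recruitment, intervention adherence, and assessment completion". The Outcome measures section turns the third into one number: "The completion rate will be assessed by the proportion of participants who complete all assessments and follow-ups". It gives no completion rate for any single instrument. The Data analysis plan adds only that feasibility and safety outcomes are shown as proportions and compared between the two groups.

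The assessments described under Outcome measures are:

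- five behavioural scales (ABC, SRS-2, CARS, ATEC, RBS-R), largely completed by parents or by interview and observation;
- saliva for four analytes: "Salivary levels of oxytocin, growth hormone, IGF-1, and IGFBP-3 are measured by ELISA", with the collection instruction "Subjects were instructed to spit at least 0.5ml of saliva into a disposable saliva collector" and a pipette as fallback;
- EEG: "Resting-state EEGs will be recorded for 10 minutes", with the condition "All the children need to be awake and relaxed during the EEG recordings";
- fNIRS: "All participants will be instructed to sit quietly for 8 minutes".

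Eligibility criteria set the age range at 2 to 10 years. The Abstract and the Discussion both say that the pilot is meant to supply data on the feasibility and design of larger trials.

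**The concern.** A pilot that informs a larger trial should tell its designers which outcomes can be obtained in this population. The instruments here place very different demands on a child. A parent questionnaire needs nothing from the child, whereas EEG and fNIRS need a cap, calm and several minutes of stillness. The protocol anticipates difficulty itself: it provides a saliva fallback, comforting of restless children and artefact removal.

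A rate that requires every assessment is limited by its hardest component. A child with all five scales, saliva and EEG but no fNIRS counts the same as a child with nothing. A low rate could make the clinical scales look hard to obtain when one recording is the obstacle. A middling rate would not tell the next trial whether to drop EEG, fNIRS or saliva.

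**Working it through.** **The plan's own figures.** The article states no expected completion rate, overall or per instrument, so there is none to reproduce. The nearest figure is the allowance for dropout in Sample size and recruitment: 20 per arm / (1 − 0.15) = 23.5, rounded up to 24, and 2 × 24 = 48. That matches the stated 48 and is not in question.

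**Number of components.** Five scales + saliva + EEG + fNIRS = 8 at a full visit.

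**Does the composite identify the failing measure?** Assume seven components at 95% and one at 60%.

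- EEG at 60%, the rest at 95%: 0.95^7 × 0.60 = 0.419.
- Saliva at 60%, the rest at 95%: 0.95^7 × 0.60 = 0.419.

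Both give 41.9% under independence. Without independence the composite lies between 7 × 0.95 + 0.60 − 7 = 0.25 and the smallest component rate, 0.60, in either case. The two situations call for different decisions in the next trial, and the endpoint reports the same value for both.

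The same holds in reverse. If 24 of 40 children (60%) complete everything, any one component could have been obtained in anywhere from 60% to 100% of that sample. The 95% Clopper-Pearson interval for the composite itself is 43.3% to 75.1%.

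**How far can the composite fall below scale completion?** The rates here are assumptions. Take all scales as obtained (100%), and EEG, fNIRS and saliva each with success rate p at one visit.

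- Independent: p^3.
- Strongest positive dependence (the same children fail everything): p.
- Lowest possible value (failures never coincide): 3p − 2.

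| p per measure | Lowest (3p − 2) | Independent (p^3) | Highest (p) | Scales |
|---|---|---|---|---|
| 95% | 85% | 86% | 95% | 100% |
| 90% | 70% | 73% | 90% | 100% |
| 85% | 55% | 61% | 85% | 100% |
| 80% | 40% | 51% | 80% | 100% |

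Under independence the composite is 14 to 49 percentage points below scale completion (100 − 86 and 100 − 51). Under the strongest positive dependence the gap is 5 to 20 points.

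**Which visit this applies to.** Under Assignment of interventions, the allocation envelope is released only after consent and baseline measures are complete. Among randomised children, baseline should therefore be close to complete by construction, and the one-visit figures are the relevant illustration. It also follows that a child who cannot manage a baseline measure may never be randomised, so a denominator of randomised children would hide failures at baseline.

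**The case against.** The strongest reply is that nothing is lost. The case report forms record baseline and post-treatment evaluations, and the mixed-effects model is fitted to each outcome, so counts per instrument can be derived later. The article does not forbid reporting them, and it attaches no progression threshold to the completion rate. This stands in part: the information will exist in the data. What remains is that the stated feasibility endpoint does not display it.

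Independence is also unlikely, because tolerance of a cap and ability to sit still affect both EEG and fNIRS. The pipette fallback, the gel-free EEG cap and the fNIRS motion correction should all raise success rates. That is fair, and it is why the figures are given as an illustration with a range. None of it affects the point that the composite cannot say which measure failed.

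Two stronger readings are tempting and are not supported.

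- A reader might infer that the rate counts procedures carried out, so that an unusable recording scores as complete. The article does not define what counts as complete. Minimum amounts of clean recording are also detail that a full protocol or analysis plan may hold.
- A reader might multiply the shortfall over baseline and end of treatment. The release of the envelope only after baseline measures rules that out for randomised children.

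**Conclusion.** The point holds as a weakness in how a feasibility endpoint is defined. As written, the only measure of assessment feasibility merges eight components and cannot show which are workable in children of this age, although informing a larger trial is the pilot's declared aim. That conclusion rests on the definition alone and needs no assumed rate.

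The size does rest on assumptions: component success of 80% to 95%, scales fully obtained, one visit. No efficacy or safety result is affected. This is an inexpensive improvement to what the pilot reports; the plan's validity does not depend on it.

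**What to change.** In Outcome measures, redefine the completion outcome as the proportion of children with data that can enter the analysis, given separately for each scale, saliva, EEG and fNIRS, and for each visit.

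- **Denominator:** consented children at baseline, so that those who cannot complete a baseline measure are counted; randomised children at every later visit.
- **Criterion for analysable data:** set for each instrument before unblinding. The 0.5 ml in the article is a volume to collect, before centrifugation, and should not be reused as a required assay volume.
- **Composite:** keep the all-assessments rate as a secondary summary.

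The cost is wording and a table; no procedure, visit or change in sample size is needed. Several proportions replace one, and each is imprecise with 40 children: 32 of 40 (80%) has a 95% Clopper-Pearson interval of 64.4% to 90.9%. EEG and fNIRS may look less favourable than under the present definition.
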